## 5. Study Method

### 5.1. Design

This is an open-label, single arm, Phase I study to evaluate the tolerability, safety, pharmacokinetics, pharmacodynamics, and antitumor effects of iPS-NKT cell in combination with auto-DC/Gal in patients with recurrent or advanced head and neck cancer who are refractory or intolerant to standard of therapy.

The dosing regimen involves both a submucosal injection of auto-DC/Gal at  $1.0 \times 10^8$  cells (fixed dose) followed by tumor-feeding arterial administration of the iPS-NKT cell at one of two dose levels: initial dose (first dose) cohort:  $3.0 \times 10^7$  cells/ $m^2$ , or second dose cohort:  $1.0 \times 10^8$  cells/ $m^2$ , administered at once, respectively. The iPS-NKT cell is administered at once five days after the DC/Gal injection. We avoid same-day administration of the investigational product to more than two subjects, and there must be a minimum interval of at least seven days before administering the investigational product to the following subject. We employed the three-by-three (3+3) design for dose escalation in this trial. Ultimately, the maximum tolerated dose (MTD) will be determined based on a total of six subjects with one or less DLT occurrences.

The screening period begins after obtaining the informed consent from each subjects. Based on the results of the screening tests, eligible subjects are registered in this study. One week prior to the start of study treatment, the subject's peripheral blood is collected, and auto-DC/Gal is manufactured (auto-DC/Gal preparation period).

DLT assessment period starts from the injection of auto-DC/Gal to 14 days after the iPS-NKT cell administration. During DLT assessment period, subjects will be carefully monitored under hospitalization. The PI or SI may leave the hospital at his/her own discretion only if the patient does not develop non-hematologic toxicity or hematologic toxicity of Grade 2 or higher and Grade 3 or higher on or after Day 7 of iPS-NKT cell administration, and be able to contact the study site and home doctor of the subjects, if any, in the event of an adverse event.

The Independent Data Monitoring Committee, consisting of members designated by the PI and study coordinating physicians, monitors the safety of the study and may make recommendations regarding the continuation of the study.

To preliminarily confirm the efficacy of the combination of iPS-NKT cells and auto-DC/Gal, tumor evaluation by contrast-enhanced CT (or MRI) will be performed prior to the start of study treatment (within 4 weeks) and on the first day of the observation period (14 days after the last administration of iPS-NKT cell or on the later of the date when the decision to discontinue administration is made).

Adverse events are observed after obtaining the informed consent until the last day of the observation period (at the time of discontinuation). If, at the end of the observation period for adverse events, an adverse event with an undeniable causal relationship to auto-DC/Gal or iPS-NKT cell has not yet recovered, the patient will be followed until the earliest point of recovery, stabilization, or death of the adverse event, whichever occurs first.

The study flow is shown below (Fig.13).

[figure not shown]

Figure 11 Study Flow

## 5.2. Dose Limiting Toxicity (DLT)

DLT is defined as the following adverse events observed during the DLT assessment period, in which a causal relationship with auto-DC/Gal or iPS-NKT cell cannot be denied. Grading is determined according to the CTCAE ver.5.0 translated in Japanese by the Japan Clinical Oncology Group (JCOG).

- 1) Grade 4 or higher hematological toxicities
- 2) any non-disease-related blood toxicity requiring any transfusion or granulocyte-colony stimulating factor (G-CSF) administration
- 3) grade 3 or higher non-hematological toxicities (excluding transient clinical laboratory abnormalities, diarrhea, nausea, vomiting, or other manageable systemic symptoms that recovered to grade 2 or below under appropriate treatments)
- 4) AEs lead to blood transfusion.

If the PI suspects the occurrence of DLTs, the PI can consult the Independent Data Monitoring Committee (IDMC), and the IDMC determines the continuation or termination for the patient. Subjects who do not complete the DLT assessment period for reasons other than DLT will not be considered DLT evaluable cases and then another

subject will be supplemented in the same dose cohort.

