| Prohibited concomitant drug and therapy          | 
 
• Corticosteroids, immunosuppressive drugs, other antineoplastic drugs, radiation therapy, or surgery including tumor resection.
 
• Any transfusion therapy (however, if the above drugs or therapies are necessary in response to an adverse event thought to be caused by DC/Gal or iPS-NKT cells, the above drugs or therapies may be used with the adverse event as DLT)
 
                                                                                                                                                                                                                                                                                                                                                                                                                                                                                                                                                                                                                                                                                                                                                                                                                                                                                                                                         |

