### 1.2.7. Expected Side Effects

The main "side effects" expected in relation to DC/Gal or iPS-NKT cells and examples of treatments are listed below.

- ① Elevated blood pressure: Antihypertensive agents should be administered according to symptoms and severity.
- ② Fever: Blood test, chest X-ray, blood culture should be performed. Regarding the possibility of infectious disease, antibiotic agents should immediately be administered. Antipyretics should not be administered if there is no febrile distress but should be given as needed if febrile distress is marked.
- ③ Respiratory distress: Administer oxygen promptly to stabilize blood oxygenation. Blood tests, X-rays and CT scan (contrast if possible) should be performed as part of the screening for the diagnosis. Possible causes of severe respiratory failure during infusion include allergic and embolic events (especially when iPS-NKT is administered). Steroids and epinephrine should be administered according to the severity of the disease, as well as antithrombotic therapy for embolism.
- ④ Shock: The physician in charge and the attending physician will respond promptly. Check vital signs, perform blood tests, and administer steroids or epinephrine according to the severity of the illness. Administer oxygen and pressor agents for respiratory failure and hypotension, depending on the severity of the illness.
- ⑤ Pharyngeal fistula: Since pharyngeal fistula associated with tumor shrinkage was observed in a previous study of combination therapy with autologous NKT cells and DC/Gal, this adverse event should be kept in mind in this study as well. If this adverse event is observed, infection prophylaxis and, if necessary, pharyngeal fistula closure should be performed.
- ⑥ Cerebral infarction: Because the cells are administered into the arteries of the neck, there is a possibility of blood clots flowing into the brain during cannulation. The patient should be evaluated after consulting a neurosurgeon for functional impairment, checking vital signs, and administering cerebro-protective drugs.
- ⑦ Bleeding and hematoma at the puncture site: This may occur with arterial puncture of the cannula. If severe hematochezia develops, consult a plastic surgeon and consider removal of hematochezia. Mild to moderate hematomas can be absorbed with observation.

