#### 5.6. Dosing schedule and route

Auto-DC/Gal and iPS-NKT cell will be administered according to the dosing schedule from subjects who meet all inclusion and exclusion criteria.

This is a FIH study on the combination therapy of auto-DC/Gal and iPS-NKT cell and will be a 3+3 design with two doses, the first and second doses. iPS-NKT cell will be administered 5 days after auto-DC/Gal injection. The number of cells administered will be  $1 \times 10^8$  cells/treatment of auto-DC/Gal and  $3 \times 10^7$  cells/m^2/treatment of iPS-NKT cells at the first dose and  $1 \times 10^8$  cells/m^2/treatment at the second dose. The number of dosing should be once for both auto-DC/Gal and iPS-NKT cell, and the dosing of the auto-DC/Gal or iPS-NKT cell in the next subject should be started after an interval of at least 7 days. Auto-DC/Gal should be administered submucosal using a microinjection syringe, and iPS-NKT cell should be administered via a catheter inserted under angiography (Selsinger method) into the tumor-feeding artery.

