## 5.10. Concomitant drugs and therapy

### 5.10.1. Permitted concomitant drug/therapy

- Palliative and supportive care for the primary disease
- Palliative radiation therapy for local pain management may be administered during the study if:
  - The irradiated area covers less than 10% of the total bone marrow
  - The irradiation field does not include the evaluation lesion
- Any transfusion therapy as a response to adverse events thought to be caused by DC/Gal or iPS-NKT cell. Such adverse events shall be considered DLT.

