### 5.10.3. Prohibited drug/therapy

In this study, DC/Gal or iPS-NKT cell will not be administered in combination with the following drugs or therapies. If it is necessary to use them clinically, it should be treated as a deviation to avoid immediate risk and reported to the record and the head of the medical institution.

- Corticosteroids (methylprednisolone 10 mg/day or more or equivalent) or immunosuppressive drugs taken or injected, other antineoplastic agents, radiation therapy, or surgery including tumor resection

- Any transfusion therapy (except as noted in 5.10.1).

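### DLT criterion 3 excludes treated, recovered systemic symptoms without capping their grade, and the synopsis and body differ on whether a related event needing steroids is a DLT

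*Protocol*

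**What the plan says.** **Criterion 3.** Section 5.2 and the synopsis count related non-haematological toxicity of Grade 3 or above as a DLT. Both exclude transient laboratory abnormalities, diarrhoea, nausea and vomiting, and end the exclusion with "or other manageable systemic symptoms that recovered to grade 2 or below under appropriate treatments". Neither place gives a maximum grade or a recovery date for the excluded symptoms, or says which symptoms are meant.

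**DLT window.** Section 5.1: "DLT assessment period starts from the injection of auto-DC/Gal to 14 days after the iPS-NKT cell administration". Section 5.6: "iPS-NKT cell will be administered 5 days after auto-DC/Gal injection".

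**Steroids.** In its row on prohibited therapy, the synopsis lists corticosteroids first, then immunosuppressants and other treatments, then transfusion. It adds that where they are needed for an event thought to be caused by either product, "the above drugs or therapies may be used with the adverse event as DLT". Section 5.10.1 permits transfusion for such events and says "Such adverse events shall be considered DLT"; it does not mention steroids. Section 5.10.3 prohibits steroids at or above 10 mg/day of methylprednisolone or equivalent and says "If it is necessary to use them clinically, it should be treated as a deviation to avoid immediate risk". Section 5.2 has no steroid criterion.

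**Expected reactions.** Section 1.2.7 names steroids among the treatments for two serious reactions. For respiratory distress: "Steroids and epinephrine should be administered according to the severity of the disease". For shock: "administer steroids or epinephrine according to the severity of the illness".

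**The concern.** The DLT rate is the only primary endpoint, and the 3+3 rule acts on the DLT count alone. Two features of the text leave that count open.

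First, the exclusion in criterion 3 applies to everything from Grade 3 upwards. Grade 5 cannot qualify because recovery is required, but Grade 4 can. A related systemic reaction that reached Grade 4 and was reversed by treatment could be left out of the primary endpoint of a first-in-human combination study.

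Second, a related event treated with steroids gets a different answer depending on which part of the protocol is followed. The question is not remote, because 1.2.7 foresees steroids for respiratory distress and shock.

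The classification also affects the individual patient. Section 5.9.1 item 1 stops iPS-NKT after a DLT, or after a Grade 3 or higher event that has not recovered by dosing. A Grade 4 reaction to DC/Gal that is read as excluded and has recovered by then meets neither condition. Whether dosing stops would rest on the other items of 5.9.1, including investigator discretion.

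**Working it through.** **1. Criterion 3, read step by step.** Take a related systemic reaction and assume that it reaches Grade 4 and falls to Grade 2 under treatment.

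- Entry: Grade 3 or above, so criterion 3 applies.
- Exclusion: if the symptom is judged manageable and systemic, it has recovered to Grade 2 or below under treatment, so it is excluded.
- Other criteria: criterion 1 is haematological. Criteria 2 and 4 need transfusion or, for criterion 2, G-CSF. None applies.
- Result: not a DLT on the broad reading. On the narrow reading, which limits the final phrase to symptoms like diarrhoea, nausea and vomiting, it is a DLT. The text does not choose between them.

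**2. The steroid rule, side by side.**

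| Place | Transfusion for a related event | Steroid for a related event | Steroid threshold |
|---|---|---|---|
| Synopsis, prohibited therapy | DLT | DLT, on the natural reading | none stated |
| 5.2 | DLT (criterion 4) | no criterion | – |
| 5.10.1 | permitted, DLT | not mentioned | – |
| 5.10.3 | refers back to 5.10.1 | deviation; DLT status not stated | 10 mg/day methylprednisolone or more |

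The synopsis sentence stands in the transfusion bullet. It refers, however, to the drugs or therapies above it, and the drugs listed above are corticosteroids, immunosuppressants and antineoplastics. It is hard to read as meaning transfusion alone.

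**3. What one event does to the decision.** The plan's own maximum reproduces: 2 doses × 6 patients = 12 (section 10.2). Section 10.5.2.1 asks for the DLT percentage per dose with a 95% confidence interval. The exact (Clopper–Pearson) limits for x DLTs in n patients are

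- lower = 2.5% point of Beta(x, n − x + 1), or 0 if x = 0
- upper = 97.5% point of Beta(x + 1, n − x)

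| Result | Rate | Exact 95% CI | Consequence under the rule |
|---|---|---|---|
| 2/6 | 33% | 4% to 78% | stop |
| 1/6 | 17% | 0.4% to 64% | tolerable |
| 1/3 | 33% | 0.8% to 91% | add three patients |
| 0/3 | 0% | 0% to 71% | no expansion triggered |

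The dose step that follows the first cohort is 1.0 × 10^8 ÷ 3.0 × 10^7 = 3.3-fold. These results need no assumed event rate. The protocol gives neither a rate of related Grade 3 or higher events nor the share that the exclusion would remove, so the change in the chance that a dose passes cannot be calculated from it.

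**The case against.** The strongest defence is that classification is not left to the wording alone. Section 7.1.3.2 requires the PI to refer suspected DLTs to the IDMC at once. Section 10.6 gives the IDMC the final judgement and has it decide on escalation from all safety information, so a Grade 4 event would be visible whatever its label. Adverse events are also tabulated by CTCAE grade (10.5.2.2). This stands as a limit on the harm. It does not settle either point: referral depends on suspicion that the event meets the 5.2 definition, 5.2 itself says only that the PI can consult, and no section gives the IDMC a grade cap or a steroid rule.

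It is also fair to say that the broad reading of criterion 3 is not the only one, and that the 3+3 consequence would follow from any misclassified event.

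Three stronger readings are tempting but unsupported:

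- A reader might infer that a reaction to DC/Gal has the whole DLT window to recover. Section 5.9.1 stops iPS-NKT for a Grade 3 or higher event that has not recovered by dosing. That rule governs dosing rather than DLT status, but it rules out this inference.
- A reader might infer that 5.10.3 says a steroid-treated event is not a DLT. It says only that the use is a deviation; an event can be both.
- A reader might infer that steroids are planned for all the systemic reactions expected. Section 1.2.7 also lists fever and raised blood pressure, which are managed without them, and steroid use for respiratory distress and shock depends on severity.

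**Conclusion.** The point holds as a gap in one definition and a mismatch between synopsis and body, both bearing on the only primary endpoint. It should be fixed. The text permits, but does not compel, a reading in which a reversed related Grade 4 systemic reaction is not a DLT. It also leaves the DLT status of a steroid-treated related event dependent on the section consulted.

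Its size is one event in a cohort of three or six, which is enough to move 2/6 to 1/6 or 1/3 to 0/3. This rests on the 3+3 rule as stated and on the natural reading of the synopsis sentence. It does not show that the wording will bias the DLT rate by any known amount, or that a dose would be escalated automatically, since the IDMC decides.

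**What to change.** **Criterion 3, in 5.2 and the synopsis.** Limit the exclusion of symptoms to Grade 3, so that any related non-haematological clinical event of Grade 4 or above is a DLT. Count a Grade 3 event as a DLT if it has not recovered to Grade 2 or below by the iPS-NKT dosing decision (events after DC/Gal) or by the end of the DLT window (events after iPS-NKT).

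**Steroids, in the synopsis, 5.2, 5.10.1 and 5.10.3.** State one rule in the same words in all four places. One workable choice is the synopsis rule with the threshold from 5.10.3: a related event needing methylprednisolone 10 mg/day or more, or equivalent, is a DLT. State in the same place how immunosuppressants are handled.

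**Cost.** The change is to wording, with the committee submission that section 12.1 requires for a protocol revision. A few more events may count as DLTs, which makes the design more cautious. Recruitment is listed from October 2022 (5.3) and the second cohort was added in version 3.0, so first-cohort events need a check against the revised wording to have both doses judged by one definition.

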### 5.3. Sample size and Study Duration

Sample Size: 2~12 cases

Study Duration: September 2022 – 03/31/2027

Recruitment: October 2022 – 02/13/2027

### 5.4. Registration of Study Site and Subject

The study sites and subjects will be registered centrally at the Data Center of Chiba University Hospital.

#### 5.4.1. Study site

- 1) After approval is obtained from the Specified Authorized Regenerative Medicine Committee of the study site, the PI shall fax a copy of the approval letter from the Specified Authorized Regenerative Medicine Committee and a request form for site registration to the Chiba University Hospital Data Center.
- 2) Chiba University Hospital Data Center will register the study site and send a notification of completion of study site registration to the PI.

#### 5.4.2. Subjects

- 1) After obtaining written consent, a screening test will be performed.
- 2) The PI or SI will confirm that subjects meet the selection criteria and do not violate the exclusion criteria regarding the screening test results.
- 3) The PI or SI will consult with at least two physicians comprising the study coordinating committee regarding the appropriateness of the judgment regarding eligibility. If the subject is finally judged "eligible," the PI, SI, or study coordinator will enroll the subject in the study.
- 4) The PI, SI, or study coordinator fills in the information necessary for subject registration and faxes it to the Chiba University Hospital Data Center. The PI or SI will confirm the eligibility and start the study treatment once the subject is determined to be eligible. Once a subject has been registered, the registration will not be cancelled. In the event that an error or duplicate registration is discovered, the Chiba University Hospital Data Center will be notified immediately.

In the event that the first dose cannot be administered within the specified period due to factors other than the subject's medical problems including fever caused by temporary infection (e.g., influenza infection), or the quality of DC/Gal or iPS-NKT cells (e.g., the cell count of DC/Gal or iPS-NKT cells was less than the expected dose). In such cases, the subject may be re-registered according to the procedures described in 3) and 4) above after conducting

the necessary screening tests again.

#### 5.5. Handling of Patients Who Are Not Registered

Subjects who are not registered for any reason, such as ineligibility, will not be included in the study subject. The PI or SI will explain to the subject that he/she is not eligible for enrollment in the study.

#### 5.6. Dosing schedule and route

Auto-DC/Gal and iPS-NKT cell will be administered according to the dosing schedule from subjects who meet all inclusion and exclusion criteria.

This is a FIH study on the combination therapy of auto-DC/Gal and iPS-NKT cell and will be a 3+3 design with two doses, the first and second doses. iPS-NKT cell will be administered 5 days after auto-DC/Gal injection. The number of cells administered will be  $1 \times 10^8$  cells/treatment of auto-DC/Gal and  $3 \times 10^7$  cells/m^2/treatment of iPS-NKT cells at the first dose and  $1 \times 10^8$  cells/m^2/treatment at the second dose. The number of dosing should be once for both auto-DC/Gal and iPS-NKT cell, and the dosing of the auto-DC/Gal or iPS-NKT cell in the next subject should be started after an interval of at least 7 days. Auto-DC/Gal should be administered submucosal using a microinjection syringe, and iPS-NKT cell should be administered via a catheter inserted under angiography (Selsinger method) into the tumor-feeding artery.

#### 5.7. Criteria for administration

For subjects enrolled in this study, auto-DC/Gal will be started after confirming that none of the "Criteria for Discontinuation of Administration" are met on the day of auto-DC/Gal or iPS-NKT cell administration.

#### 5.8. Criteria for postpone

If any of the following criteria are met, the PI or SI may postpone the administration of iPS-NKT cells for up to 3 days.

- 1) When the PI or SI determines that administration of auto-DC/Gal or iPS-NKT cell is inappropriate.
- 2) All adverse events occurring after the administration of DC/Gal or iPS-NKT cell do not recover to a manageable Grade 2 or Grade 1 or below, or to baseline.
- 3) Infectious disease requiring treatment develops within 24 hours prior to administration of DC/Gal or iPS-NKT

cell, including cases of fever of 38°C or higher.

## 5.9. Criteria of treatment and study discontinuation for each subject

### 5.9.1. treatment discontinuation

If any of the following criteria are met, the PI or SI will discontinue administration of DC/Gal or iPS-NKT cell. If administration is discontinued, the subject will be shifted to the observation period from the date when the decision to discontinue administration was made, and testing and assessment will be continued in accordance with the study schedule.

- 1) DLT occurs after administration of DC/Gal, or all adverse events of Grade 3 or higher that occurred during the study period do not recover or improve to Grade 1 or clinically manageable Grade 2 by the time immediately before administration of DC/Gal or iPS-NKT cell.
- 2) Subject develops an infectious disease requiring treatment that does not recover or improve to Grade 1, or does not improve to a clinically manageable Grade 2 by the time immediately prior to administration of DC/Gal or iPS-NKT cell.
- 3) SpO2 (room air) is maintained below 90%.
- 4) Grade 2 or higher on the mMRC shortness of breath scale (see Appendix 3) in the examination before administration of DC/Gal or iPS-NKT cells.
- 5) Requirement for the discontinuation from the subject.
- 6) Other cases in which the need to discontinue the administration of DC/Gal or iPS-NKT cell to the subject are recognized by the PI or SI.

The PI or SI should record the date of discontinuation, reason for discontinuation, and other necessary information.

In the case of discontinuation of DC/Gal or iPS-NKT cell administration, the "date of discontinuation" is not the date when the event causing the discontinuation occurred or became known, but the date when the PI or SI decided to discontinue.

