| Criteria for administration             | 
For patients enrolled in the study, administration of the auto-DC/Gal or the iPS-NKT cells will be initiated after confirming that none of the "Criteria for Discontinuation of Administration" are met on the date of DC/Gal or iPS-NKT cell administration.
                                                                                                                                                                                                                                                                                                                                                                                                                                                                                                                                                                                                                                                                                                                                                                                                                                                                                                                                                                                                                                                                                                                                                                                                                                                                                                                                                                                       |

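### Section 5.9.1 item 1 words the mandatory Grade 3 dosing stop as all events not recovering, where any unrecovered event is evidently meant

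*Protocol*

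**What the plan says.** Section 5.9.1 of the protocol lists six criteria; meeting any one of them means that the investigator will discontinue DC/Gal or iPS-NKT. Item 1 has two limbs. The first is a DLT after DC/Gal. The second is that "all adverse events of Grade 3 or higher that occurred during the study period do not recover or improve to Grade 1"; a clinically manageable Grade 2 is accepted too, and the judgement is made just before dosing. The suspension row of the synopsis repeats this wording.

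Item 2 is put in the singular: "Subject develops an infectious disease requiring treatment that does not recover or improve to Grade 1". Item 6 is a catch-all: "Other cases in which the need to discontinue the administration of DC/Gal or iPS-NKT cell to the subject are recognized" by the investigator.

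The list is operative. Section 5.7 requires confirmation that none of the criteria "are met on the day of auto-DC/Gal or iPS-NKT cell administration". The synopsis row on administration says that "administration of the auto-DC/Gal or the iPS-NKT cells will be initiated after confirming that none of the" discontinuation criteria apply.

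Section 5.8 item 2 and the synopsis deferral row use the same all-do-not-recover construction for postponement of up to 3 days, but there the investigator may postpone and is not obliged to.

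**The concern.** A universal subject with a negated verb can be read in two ways: none has recovered, or not all have recovered. For a stopping rule these give different decisions. On the literal reading, one Grade 3 event that has resolved removes the automatic stop for a different Grade 3 event that is still running. Nothing elsewhere in the protocol states which reading applies, and the synopsis repeats the sentence without settling it.

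This is a first-in-human combination in which each product is given once, the second by arterial infusion. A mandatory stop in that setting should give the same answer to every investigator and to a monitor checking compliance. At stake is whether one particular stop is automatic or discretionary. No endpoint, sample size or estimate is involved.

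**Working it through.** The protocol has no figure to reproduce here; this is a comparison of texts.

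**1. Where the readings differ.** Let n be the number of Grade 3 or higher events so far, and u the number not yet recovered to Grade 1 or manageable Grade 2 at the check.

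- Intended reading (not all recovered): stop if u ≥ 1.
- Literal reading (none recovered): stop if n ≥ 1 and u = n.

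| n | u | Intended | Literal |
|---|---|---|---|
| 1 | 0 | dose | dose |
| 1 | 1 | stop | stop |
| 2 | 0 | dose | dose |
| 2 | 1 | stop | dose |
| 2 | 2 | stop | stop |

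They differ only when 1 ≤ u < n, which needs at least two events with a mixed outcome.

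**2. Remove the cases that the DLT limb catches.** Under Section 5.2 a DLT must be an event "in which a causal relationship with auto-DC/Gal or iPS-NKT cell cannot be denied", within the DLT period. The basic haematological threshold is "Grade 4 or higher hematological toxicities"; a lower grade counts only if it leads to transfusion or G-CSF. So an ongoing unrelated Grade 3 event is not a DLT, and neither is a Grade 3 haematological event managed without transfusion or G-CSF.

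**3. Remove the cases that other criteria catch.** Items 2 to 5 cover unrecovered infection, SpO2 below 90%, mMRC Grade 2 or higher, and the subject's own request. For any other ongoing event, what remains is item 6 of 5.9.1 (stop) or item 1 of 5.8 (postpone). Both depend on the investigator's judgement.

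**4. When it can arise.** DC/Gal is given on Day 1 and iPS-NKT on Day 6. The mixed case is mainly a matter for the Day 6 check, because Section 8.1 defines adverse events as occurring after administration.

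**5. Can it be sized?** The protocol gives neither a Grade 3 rate nor a recovery fraction, so any figure rests on assumptions. Suppose non-DLT Grade 3+ events before iPS-NKT are Poisson with mean L per subject, and each has recovered with probability r. The mixed-case probability is

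p = (1 − e^(−Lr)) × (1 − e^(−L(1−r))), largest at r = 0.5.

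- L = 0.05: p = (1 − e^(−0.025))² = 0.061%; at least one in 12 subjects, 1 − (1 − p)^12 = 0.7%.
- L = 0.3: p = (1 − e^(−0.15))² = 1.94%; at least one in 12, 21.0%.

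If those rates are taken to cover Day −42 to Day 6 (42 + 5 = 47 days, no Day 0) and are scaled to the 5 days from Day 1 to Day 6, L becomes 0.0053 to 0.032. Then p is 0.0007% to 0.025%, and the chance of at least one case in 12 is 0.009% to 0.30%.

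The upper ends differ by a factor of 21.0 / 0.30 = 70, depending only on the window assumed. No single figure is supportable.

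**The case against.** The strongest reply is that nobody would apply the literal reading. It has no clinical rationale, item 2 points the other way, and the phrase is awkward but recognisable English for not all having recovered. The document is visibly a translation from Japanese, so the operative text may be clear. Existing controls also help. Related Grade 3 non-haematological events are DLTs, apart from the listed exclusions. Subjects are hospitalised in the DLT period with daily adverse event checks. Item 6 obliges a stop once the investigator recognises the need.

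Most of this stands, and it is why the point is minor. It does not remove the defect. The current text is the rule in the document at hand, and it appears in this form in four places. Item 6 binds only after a judgement has been made, so it does not restore an automatic trigger. If the Japanese text is clear, the correction simply brings the English into line.

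A reader might also infer a longer exposure, with events from consent onward affecting the DC/Gal check as well. Section 8.4 does collect adverse events from consent, but Section 8.1 defines them as occurring after administration. The protocol leaves that conflict open, so the longer window should not be relied on.

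**Conclusion.** The point holds as a minor ambiguity in operative safety text. In one configuration (two or more Grade 3+ events, at least one recovered and another ongoing that is not a DLT), a stop evidently meant to be automatic is left to investigator judgement. With a single such event the readings agree.

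The case should be rare. That judgement rests on the need for two such events, mainly in the days between the two products. The calculated percentages rest on assumed rates, and the 21% figure combines the highest assumed rate, the least favourable recovery split and all 12 subjects. It is not an estimate.

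Two stronger inferences are not supported. The protocol does not set out to allow dosing over ongoing Grade 3 toxicity: item 2 and the rest of the list point to the opposite intent. Nor is the DLT rate, its confidence interval or the 3+3 rule affected, since none of them is defined through this sentence.

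**What to change.** In 5.9.1 item 1 and the synopsis suspension row, change the subject to *any adverse event* and the verb to *has not recovered or improved*. Keep the grade threshold, the reference to the study period, the recovery level and the timing as they are. Make the parallel change in 5.8 item 2 and the synopsis deferral row, and leave postponement optional there.

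The cost is a wording change in four places at the next amendment. The one downside is that, rarely, an infusion is withheld that the literal wording would have allowed. Section 5.2 already provides for a subject who then fails to finish the assessment period: "Subjects who do not complete the DLT assessment period for reasons other than DLT will not be considered DLT evaluable cases", and another subject is added to the cohort. Whether the differently worded exclusion in 10.1.1 fits every such case is a separate question that this change does not settle.
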